## Abstract

**Background:** Intravenously administered indocyanine green (ICG) accumulates in lung tumors, facilitating their detection via a fluorescence spectrum measurement. This method aids in identifying tumor locations that are invisible to the naked eye. We aim to determine the optimal ICG dose and administration method for accurate tumor identification during lung resection surgeries, utilizing a novel ICG fluorescence spectroscopy system for precise tumor localization. **Materials and Methods:** ICG should be dissolved in the provided solution or distilled water and administered intravenously approximately 24 h before surgery, beginning with an initial dose of 0.5 mg/kg. If the tumor detection rate is insufficient, the dose may be gradually increased to a maximum of 5.0 mg/kg to determine the optimal dosage for effective tumor detection. This fluorescence spectroscopy during surgery may reveal additional lesions that remain undetected in preoperative assessments. The primary endpoint includes the correct diagnostic rate of tumor localization. The secondary endpoints include the measurement of the intraoperative ICG fluorescence spectral intensity in lung tumors, the assessment of the operability and safety of intraperitoneal ICG administrations, the measurement of the ICG fluorescence spectral intensity in surgical specimens, the comparison of the spectral intensity in lung tissues during collapse and expansion, the correlation between ICG camera images and fluorescence spectral intensity, and the comparison of fluorescence analysis results with histopathological findings. The trial has been registered in the jRCT Clinical Trials Registry under the code jRCTs011230037. **Results and Conclusions:** This trial aims to establish an effective methodology for localizing and diagnosing malignant lung tumors, thereby potentially improving surgical outcomes and refining treatment protocols.

## 1. Introduction

Lung cancer is the leading cause of cancer-related deaths worldwide. The advent of widespread computed tomography (CT) screening has significantly increased the detection rate of lung cancer, enabling its early intervention and potentially improving patient outcomes [1]. Traditionally, the standard treatment for lung cancer involves lobectomy and lymph node dissection. However, for small and early stage tumors, partial resection is increasingly preferred to preserve lung function [2].

Accurate localization is particularly challenging in minimally invasive procedures, such as video-assisted thoracic surgery (VATS), where the ability to palpate the tumor is limited. This challenge is further exacerbated in robot-assisted thoracic surgery and uniportal VATS.

Various techniques have been reported for localizing lung tumors during thoracoscopic surgery. Preoperative methods include CT-guided percutaneous localization [3], transbronchial localization, ultrasound-guided localization, and 3D-CT-guided localization [4]. Recently, virtual-assisted lung mapping has emerged for clinical application [5]. Intraoperative approaches include the staining and marking of lung tumors using methods such as intraoperative stamping and CT-guided localization [6,7]. Traditional localization methods, including preoperative CT-guided marking and intraoperative staining, often result in complications such as dye diffusion, implant displacement, and radiation exposure. These challenges underscore the need for less invasive and more efficient techniques.

Indocyanine green (ICG), a water-soluble dye that emits fluorescence under near-infrared light, presents a significant advancement in tumor localization and lung segmentation during surgeries. Its application in thoracoscopy is gaining traction due to the enhanced precision it offers in surgical procedures, without the negative side effects typically associated with traditional techniques [8,9,10,11]. Notably, while intravenous ICG administration is commonly employed in thoracic surgeries to delineate resection margins, the specific use of intravenous ICG for tumor identification has been explored primarily in clinical trials, with limited application in routine clinical settings [12,13]. Moreover, the percutaneous or transbronchial methods of ICG marking, though practiced in a select few institutions, are complex procedures marked by concerns over their invasiveness and potential complications [3,5].

Given these considerations, the spectral measurement system we propose, designed for intravenous application, stands to not only enhance the existing utilization of ICG in thoracoscopic surgeries but also address the limitations and challenges associated with current ICG marking techniques [14].

We developed an innovative ICG fluorescence spectroscopy system designed for precise tumor localization [15]. This system can measure the spectrum of near-infrared light emitted by ICG in tumor tissues, offering a new dimension to surgical navigation. The introduction of a fluorescence spectrum measurement system that detects ICG emissions invisible to the naked eye marks a significant advancement. This technology has the potential to revolutionize surgical navigation by accurately identifying tumors deep within the lung tissue, thereby enhancing the precision of thoracoscopic surgery. As this technology awaits clinical application, it underscores the ongoing evolution towards more precise and minimally invasive surgical interventions for lung cancer treatment. 

This study investigates the application of ICG and fluorescence spectral measurements in thoracoscopic surgery to enhance the accuracy of visual tumor localization. Utilizing a novel ICG fluorescence spectroscopy system, we aim to determine the optimal ICG dose and administration method for accurate tumor identification during lung resection surgeries.

## 2. Experimental Design and Detailed Procedure

### Study Design

This is a single-center, open, dose-comparison control, interventional clinical trial.

The trial has been registered in the jRCT Clinical Trials Registry under the code jRCTs011230037 (https://jrct.niph.go.jp/en-latest-detail/jRCTs011230037) (accessed on 28 March 2024).

The detailed procedure is described in Figure 1.

The data obtained will be used for analysis until 1 August 2026. Subsequently, the data will be stored and may be used for future studies.
(1)Dissolve indocyanine green (ICG) (Diagnogreen^®^, Daiichi-Sankyo, Tokyo, Japan) in 5 mL to 10 mL of the attached injection solution, dilute it with 200 mL of saline solution to make a total volume of approximately 205–250 mL, and inject it intravenously the day before surgery (approximately 24 h (window of 22 to 26 h) before the surgery) over approximately 1–2 h. The dose should be in the range of 0.5 mg/kg to 5.0 mg/kg. The initial dose should be 0.5 mg/kg. If the positive diagnosis rate is low, the dosage should be increased at 1.0 mg/kg intervals to a maximum of 5.0 mg/kg to determine the optimal dosage for detecting tumors.(2)The probe of the fluorescence spectroscopy system is used in the thoracic cavity, and the ICG is excited by the excitation light source when the probe is applied to the lung tumor to observe whether a fluorescence wavelength is detected. Measure the distance from the surface of the lung to the probe, and the distance from the surface of the lung to the tumor.(3)Pulmonary lobectomy and more extensive surgical approaches are performed as usual in our department. The probe of the fluorescence spectroscopy system is applied to the resected lung removed from the thoracic cavity to generate ICG fluorescence using an excitation light source to determine if the fluorescence wavelength is detected.(4)Postoperative observation of patient for 1 to 2 weeks.

## 3. Materials and Equipment

### 3.1. Fluorescence Spectroscopy System

The near-infrared fluorescence spectroscopy system developed by the Advantest Corporation in Tokyo (https://www.advantest.com/) (accessed on 28 March 2024) is designed to detect the spectrum of near-infrared light [15]. It received clinical approval for use in the human body, specifically for intraperitoneal administration, in February 2023 (approval number: 30500 BZX00031000). Unlike traditional near-infrared thoracoscopes that rely on visual confirmation of ICG excitation, this advanced system can detect ICG emissions that are invisible to the naked eye by capturing the specific wavelengths emitted by ICG. This capability is particularly valuable for identifying ICG deposits deep beneath the lung surface, where emissions may not be visually detectable.

### 3.2. Lumifinder™ MED7100

Generic name: ICG fluorescence observation device (JMDN code: 71076002).

Classification: controlled medical device (Class II), specified maintenance control medical device.

Medical device approval number: 30500BZZZX00031000.

Dimensions: approx. 390 (W) × 250 (H) × 400 (D) mm.

Weight: 30 kg or less.

Power supply: AC100 v 50/60 Hz.

Power consumption: 170 VA.

Type of protection against electric shock: Class I.

Degree of protection against electric shock: BF-type mounting part.

Operating environment Temperature range: 10–30 °C.

      Humidity range: 30–80%

      Air pressure range: 700~1060 hPa

Scope Insertion diameter: 10 mm.

      Effective length of insertion part: 288.9 mm

      Beam direction: 0°

      Beam angle: 25.4°

Laser Specifications: excitation wavelength—785 ± 10 nm, power—40 mW max.

Guiding light: wavelength—520 ± 10 nm, power—10 mW max.

Laser class: 3R.

### 3.3. Allocation Method

The initial ICG dose will be 0.5 mg/kg. Thereafter, the dose will be increased to 1.0 mg/kg, 2.0 mg/kg, and so on, at 1.0 mg/kg intervals to a maximum of 5.0 mg/kg. In this study, the lowest dose of ICG used for blood flow evaluations during the segmentectomy of the lungs and liver was 0.5 mg/kg. Additionally, for the purpose of a safety evaluation, a minimum dose of 0.5 mg/kg was established. Ten patients will be allocated this in order from the lowest dose, resulting in a total sample size of 60 patients.

The sensitivity and specificity of tumor detection at each dose will be calculated using the following formulae.

Sensititvity = number of cases in which tumors were identified by the fluorescence spectroscopy system/total number of cases in which pathology resulted in a diagnosis of malignancy.

Specificity = number of cases in which no tumor was identified by the fluorescence spectroscopy system/total number of cases in which pathology showed a benign tumor.

The most suitable dose for tumor detection will be determined by taking into consideration both accuracy and dosage. While the maximum dose is 5.0 mg/kg, if the positive detection rate becomes 0.9 or higher at a certain dose, and improvement in the positive detection rate cannot be expected further by increasing the dose thereafter, the dosage should not be increased. 

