### 3.7. Basis for Setting the Target Number of Cases

We defined the positive diagnosis rate as the proportion of accurately identified malignant or benign cases to the total number of cases examined. Anticipating a positive diagnosis rate of 0.9, we determined that a minimum of ten cases per dosage level will be required. This sample size ensures a 70% probability of estimating the positive diagnosis rate with a margin of error not exceeding 0.4, within a 95% confidence interval. Thus, given the inclusion of up to six different dosage levels in our study, the total sample size could reach up to 60 cases.

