### 3.8. Statistical Analysis Methods

The data obtained will be summarized using summary statistics (mean, standard deviation, median, and interquartile range) or frequencies and percentages, both overall and stratified by dose. For each dose, estimates of the positive diagnostic rate, sensitivity, specificity, and 95% confidence intervals will be calculated based on the Wilson score method. In addition, the mean and 95% confidence intervals of the numerical values of wavelength intensity in the peak range of the ICG fluorescence wavelengths will be calculated and compared between doses using an analysis of variance. Subgroups, such as expanded vs. collapsed lungs and non-tumor vs. tumor areas, will also be examined. Adverse events will be presented as the number of occurrences per dose.

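### Sensitivity and specificity are defined with numerators not restricted by pathology, so false positives inflate sensitivity and missed cancers inflate specificity

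*Protocol article*

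**What the plan says.** Section 3.3 (Allocation Method) of the protocol article states that sensitivity and specificity at each dose will be computed from two formulas.

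- Sensitivity: the ratio is "number of cases in which tumors were identified by the fluorescence spectroscopy system/total number of cases in which pathology resulted" in malignancy.
- Specificity: the numerator is the "number of cases in which no tumor was identified by the fluorescence spectroscopy system" and the denominator is the "total number of cases in which pathology showed a benign tumor".

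Section 3.8 (Statistical Analysis Methods) then plans, for each dose, that "estimates of the positive diagnostic rate, sensitivity, specificity, and 95% confidence intervals will be calculated based on the Wilson score method".

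Section 3.7 (Basis for Setting the Target Number of Cases) defines a third measure, the positive diagnosis rate, as the "proportion of accurately identified malignant or benign cases to the total number of cases examined". That definition does tie the device result to pathology.

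**The concern.** Sensitivity is a proportion among malignant cases and specificity a proportion among benign cases. In each, the numerator must be a subset of the denominator. In section 3.3 the pathology condition appears only below the line. The sensitivity numerator therefore takes in benign lesions that the system called positive, and the specificity numerator takes in cancers that it missed. No other section restricts the numerators.

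Benign cases are to be expected: Table 1 admits patients whose tumor is only suspected, and sections 3.3 and 3.7 both provide for benign findings. At stake are the per-dose accuracy figures the trial will report. Followed literally, the formulas could show a dose as perfect although the system made errors at that dose, or return a rate above 100% with no confidence interval.

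**Working it through.** **Notation.** TP and FN are malignant cases with and without a tumor identified by the system. FP and TN are benign cases with and without a tumor identified. M = TP+FN, B = FP+TN, N = M+B. Every case is assumed to have a device result and a malignant or benign pathology result.

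**The plan's own figure.** Section 3.7 asks for 10 cases per dose, at an anticipated positive diagnosis rate of 0.9, for a 70% probability of meeting a 0.4 precision target with a 95% interval. Reading 0.4 as the total width of the Wilson interval, at n = 10 the width is 0.386 for 9 correct, 0.278 for 10 correct and 0.453 for 8 correct. The target is therefore met with 9 or 10 correct:

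10 × 0.9⁹ × 0.1 + 0.9¹⁰ = 0.387 + 0.349 = 0.736.

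For n = 7, 8 and 9 the probabilities are 0.478, 0.431 and 0.387. The figure of 10 is reproduced on this reading. It rests on (TP+TN)/N and does not use the section 3.3 formulas.

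**Formulas as written against the standard ones.**

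- Sensitivity as written = (TP+FP)/M = TP/M + FP/M, which is the correct value plus FP/M.
- Specificity as written = (TN+FN)/B = TN/B + FN/B, which is the correct value plus FN/B.

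Each false positive adds 1/M to sensitivity, and each missed cancer adds 1/B to specificity. The bias is never downward. It is zero for sensitivity only if FP = 0, and for specificity only if FN = 0.

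**Illustrations for 10 patients.** The documents give no malignant/benign split, so all splits here are assumptions.

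| M/B | TP, FN, FP, TN | Sensitivity: written / correct | Specificity: written / correct | (TP+TN)/N |
|---|---|---|---|---|
| 9/1 | 8, 1, 1, 0 | 9/9 = 100% / 88.9% | 1/1 = 100% / 0% | 80% |
| 9/1 | 9, 0, 1, 0 | 10/9 = 111% / 100% | 0/1 = 0% / 0% | 90% |
| 8/2 | 7, 1, 1, 1 | 8/8 = 100% / 87.5% | 2/2 = 100% / 50% | 80% |
| 8/2 | 6, 2, 1, 1 | 7/8 = 87.5% / 75% | 3/2 = 150% / 50% | 70% |
| 5/5 | 4, 1, 2, 3 | 6/5 = 120% / 80% | 4/5 = 80% / 60% | 70% |

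**Consistency with section 3.7.** With correct formulas, M/N × sensitivity + B/N × specificity = (TP+TN)/N. In the first row, 0.9 × 8/9 + 0.1 × 0 = 0.80. With the formulas as written, the same weighted sum is (TP+FP+TN+FN)/N = 1, whatever the system's performance. So, when both classes are present, both written rates are 100% if FP = FN, and otherwise one of them exceeds 100%. In the first and third rows, 100% and 100% would stand beside 80% accuracy from the same patients.

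**Wilson interval.** Take a numerator of n+j over a denominator n, with j ≥ 1. The term under the square root, p(1−p)/n + z²/(4n²), equals (1/n²) × [z²/4 − j(n+j)/n]. At 95%, z²/4 = 0.96, while j(n+j)/n = j + j²/n is greater than 1. The term is always negative, so no interval exists. For 10/9 the bracket is 0.96 − 1.11 = −0.15.

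**The case against.** The strongest reply is that this is elliptical drafting and not a planned wrong estimator. Sensitivity and specificity are standard terms. The Wilson method presupposes a numerator contained in its denominator. Section 3.7 shows that the authors do tie the device result to pathology. An analyst reading these sections together would probably compute TP/(TP+FN) and TN/(TN+FP), and a rate above 100% would expose the literal reading at once.

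Much of this stands: the remedy is one of wording, and the intention was probably right. It does not remove the point. Section 3.3 states the formulas as the way the rates will be calculated, so this is not a detail left to a fuller document. The literal reading also gives no warning when FP and FN are equal and above zero, because both rates then show 100%.

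It is also fair to say that sensitivity and specificity are not named among the endpoints in section 3.4. The primary endpoint there, the correct diagnostic rate, is most naturally the rate defined in section 3.7.

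A reader might infer that the faulty rates decide the dose, because the formulas stand directly before the dose-choice text. Section 3.3 does not say so. It refers to accuracy together with dosage, and to a positive detection rate of 0.9, and equates neither term with sensitivity or specificity. The nearest defined quantity is the positive diagnosis rate of section 3.7, which has the same 0.9 figure and is correctly defined.

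A reader might also infer that each formula rewards the very error it is meant to penalise. It does not. A missed cancer still lowers sensitivity and a false positive still lowers specificity. The fault is that each formula adds the other kind of error.

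**Conclusion.** The formulas in section 3.3 are wrong as written and should be corrected. Sensitivity is overstated by FP/M and specificity by FN/B, either can exceed 1 and then has no Wilson interval, and the pair can conflict with the positive diagnosis rate of section 3.7. The direction of the bias follows from the text alone. Its size depends on the malignant/benign split and the error counts, which the documents do not give. Under the assumed splits where both written rates are 100%, the correct values are 88.9% and 0% (9/1) or 87.5% and 50% (8/2). Specificity is the more fragile of the two when benign cases are few, because one missed cancer adds a full 1/B.

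The positive diagnosis rate and the 10-per-dose sample size are unaffected. An effect on dose escalation or dose choice is conditional: it arises only if accuracy or positive detection rate in section 3.3 is taken to mean these measures.

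**What to change.** Replace the two formulas in section 3.3 with:

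- Sensitivity = pathologically malignant cases in which the system identified a tumor / all pathologically malignant cases.
- Specificity = pathologically benign cases in which the system identified no tumor / all pathologically benign cases.

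If the statistical analysis plan, which is not shown, repeats the formulas, make the same change there. The cost is two lines of wording, with no change to sample size, conduct or data collection. Reported sensitivity and specificity may be lower than under the present wording, and specificity substantially lower where a dose group has few benign cases.

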### 3.4. Endpoints

The primary endpoint of the study is the correct diagnostic rate for tumor localization using an intravenous ICG administration. The secondary endpoints include the measurement of intraoperative ICG fluorescence spectral intensity in lung tumors, the assessment of operability and safety when ICG is used intraperitoneally, the measurement of ICG fluorescence spectral intensity in surgical specimens, the comparison of the spectral intensity in lung tissues during collapse and expansion, the correlation between ICG camera images and fluorescence spectral intensity, and the comparison of fluorescence analysis results with histopathological findings from surgical specimens.

Safety endpoints include the evaluation of adverse events identified after the administration of the study drug.

### 3.5. Study Patients and Eligibility Criteria

Patients attending or being admitted to the Department of Thoracic Surgery, Hokkaido University Hospital, and deemed suitable for surgery by the department will be enrolled in this study.

The eligibility criteria are shown in Table 1.

### 3.6. Target Number of Patients

A maximum of 60 patients will be enrolled, including 10 patients per dosage level.

### 3.7. Basis for Setting the Target Number of Cases

We defined the positive diagnosis rate as the proportion of accurately identified malignant or benign cases to the total number of cases examined. Anticipating a positive diagnosis rate of 0.9, we determined that a minimum of ten cases per dosage level will be required. This sample size ensures a 70% probability of estimating the positive diagnosis rate with a margin of error not exceeding 0.4, within a 95% confidence interval. Thus, given the inclusion of up to six different dosage levels in our study, the total sample size could reach up to 60 cases.

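### Section 3.7 calls 0.4 a margin of error, but the 70% and the minimum of ten per dose reproduce only if 0.4 is the full width of the 95% interval

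*Protocol article*

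**What the plan says.** Section 3.7 of the protocol article (Basis for Setting the Target Number of Cases) defines the positive diagnosis rate as "the proportion of accurately identified malignant or benign cases to the total number of cases examined". It then gives the design values: "Anticipating a positive diagnosis rate of 0.9, we determined that a minimum of ten cases per dosage level will be required". The precision behind that number is described in one sentence, which says that the sample size "ensures a 70% probability of estimating the positive diagnosis rate with a margin of error not exceeding 0.4"; the limit is tied to a 95% confidence interval. The total follows: "given the inclusion of up to six different dosage levels in our study, the total sample size could reach up to 60 cases".

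Section 3.8 (Statistical Analysis Methods) names the interval for this rate at each dose: "95% confidence intervals will be calculated based on the Wilson score method".

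The article nowhere defines margin of error as the full width of an interval.

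**The concern.** Four numbers in section 3.7 are meant to fit together: a true rate of 0.9, ten patients, a probability of 70% and a limit of 0.4. Given the interval method, any three should determine the fourth. In ordinary usage a margin of error is the distance from the middle of the interval to either end. For ten patients a half-width of 0.4 is so loose that no result could exceed it, and a far smaller group would also meet it. The sentence as worded therefore does not support the number that it is there to support.

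This sentence is the only justification given for ten per dose and up to 60 in total. A reader of the protocol or the final report would take the aim to be an interval of plus or minus 0.4. Every possible result meets that aim, so it says nothing about the precision that was planned.

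**Working it through.** **Inputs.** True rate p = 0.9, n = 10 per dose, target probability 70% and limit 0.4 (all section 3.7); 95% Wilson score interval (section 3.8). The interval is taken as two-sided, so z = 1.96 and z² = 3.8415.

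**Formulas.** For x correct out of n, with r = x/n:
- centre = (r + z²/(2n)) / (1 + z²/n)
- half-width h = z·√(r(1−r)/n + z²/(4n²)) / (1 + z²/n)
- full width = 2h

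The probability of meeting a limit is the sum of the binomial probabilities, X ~ Bin(n, 0.9), over all x that meet it.

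**Step 1: reproduce the plan's figure, reading 0.4 as the full width.** At n = 10, 1 + z²/n = 1.384.

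| Result | 95% Wilson interval | Full width | At most 0.4? |
|---|---|---|---|
| 8/10 | 0.490 to 0.943 | 0.453 | no |
| 9/10 | 0.596 to 0.982 | 0.386 | yes |
| 10/10 | 0.722 to 1.000 | 0.278 | yes |

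For 9/10: h = 1.96·√(0.09/10 + 3.8415/400)/1.384 = 0.193, so the width is 0.386.

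Results of 5 to 7 out of 10 give wider intervals than 8/10. Results below 5 mirror those above it, so the only others that meet the limit are 0/10 and 1/10, whose probability at p = 0.9 is negligible. Hence

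P(width ≤ 0.4) = P(X ≥ 9) = 10·0.9⁹·0.1 + 0.9¹⁰ = 0.3874 + 0.3487 = 0.736.

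Smaller numbers:

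| n | P(full width ≤ 0.4) |
|---|---|
| 5 or fewer | 0 |
| 6 | 0.531 |
| 7 | 0.478 |
| 8 | 0.431 |
| 9 | 0.387 |
| 10 | 0.736 |

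Ten is the smallest number that reaches 70%. Both the minimum of ten and the 70% threshold are recovered.

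**Step 2: the literal reading, 0.4 as the half-width.** The Wilson half-width is largest at r = 0.5, where the formula reduces to z/(2√(n + z²)). At n = 10 this is 1.96/(2·√13.84) = 0.263, so P(half-width ≤ 0.4) = 100%. At n = 3 the same expression gives 1.96/(2·√6.84) = 0.375. It falls as n grows, so the limit is met with certainty at every n from 3 upward. At n = 2 the probability is 0.82 (1 of 2 gives 0.4055, just over). Even n = 1 meets the limit, with half-width z²/(2(1 + z²)) = 0.397.

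**Step 3: can another reading rescue the wording?** Taking the margin as the larger distance from the estimate to either limit also gives 100% at n = 10; the maximum is 0.310, at 8/10. Continuity-corrected Wilson, Clopper-Pearson, Wald, Agresti-Coull and Jeffreys intervals all give 100% for a half-width of at most 0.4 at n = 10. For the full width at n = 10, Jeffreys and untruncated Wald also give 0.736, while Clopper-Pearson, Agresti-Coull and continuity-corrected Wilson give 0.349. What matters is width against half-width, and the method that the article names reproduces the design.

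**The case against.** The strongest reply is that nothing of substance is wrong. Taken as a lower bound, the literal sentence is true: a probability of 100% is at least 70%. The number of patients is the one that the intended calculation requires. Nothing later in the article uses the 0.4: the dose rule in section 3.3 turns on the detection rate, and the intervals in section 3.8 are computed in the same way under either reading. All of this stands and sets the size of the point. It does not rescue the sentence as a reason for ten, because under its literal meaning ten is not the minimum.

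A reader might infer more than the documents support:

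- **That precision is overstated or the groups are too small.** The reverse holds. A half-width of 0.4 would be an interval up to 0.8 wide, against an intended full width of at most 0.4.
- **That nobody could check whether the precision aim was met.** Section 3.8 fixes the method and level, so each dose's interval can be computed and compared with 0.4 under either reading.
- **That the intended precision is plus or minus 0.2.** The half-width is at most 0.2, but the interval is not centred on the estimate. At 9/10 the lower limit lies 0.304 below 0.9 and the upper limit 0.082 above it.
- **That losing one patient ruins the design.** At n = 9 the probability is 38.7%, but it moves in a saw-tooth because the outcomes are discrete: 0.697 at n = 11, 0.659 at n = 12 and 0.866 at n = 13. Quoting n = 9 alone would be one-sided.

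**Conclusion.** The point holds as a minor correction to a stated figure. Section 3.7 gives the full width of the 95% interval the name of its half-width. Under the literal meaning the probability at ten patients is 100%, not 70%; under the full-width meaning it is 73.6%, and ten is the smallest number that reaches 70%. The error is conservative, and ten per dose with a maximum of 60 stands.

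The conclusion assumes a two-sided Wilson interval, a true rate of exactly 0.9, ten evaluable patients at the dose, and 70% as the threshold to be reached rather than the probability achieved. If 70% was meant as the achieved value, it should read about 74%. Because of the saw-tooth, minimum means the smallest number that reaches 70%; it does not mean that every larger number does.

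**What to change.** Replace the precision sentence in section 3.7 with wording such as:

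> With 10 evaluable patients per dose and a true positive diagnosis rate of 0.9, the probability that the full width of the two-sided 95% Wilson interval does not exceed 0.4 is about 74%; 10 is the smallest number for which this probability reaches 70%.

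State the width and do not convert it to plus or minus 0.2. If the full protocol or the statistical analysis plan, neither of which is shown, repeats the sentence, correct it there too. The cost is one sentence, with no extra patients and no change to the design or analysis.
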